### Plans to promote participant retention and complete follow-up {18b}

Potential participants will be educated on study procedures during the consent process and screening visit to help with adherence and understanding of the study. Various study retention techniques will be used throughout the study such as reminder calls and reimbursement for study visits to keep participants engaged in the study. Compensation is as follows:

**Table Tabb:** 

Study activities	In-person visits + travel/parking	Virtual visits	CAROMA/Med compliance	Study completion
Payment	$75 (per visit)	$10 (per visit)	$5 (per day)	$100
Participants can earn up to $740, if they complete all study procedures				

### Data management {19}

The study will use Research Electronic Data Capture (REDCap) to store and database all electronic research data. Source documentation will be collected on hardcopy CRFs and entered into REDCap by research staff at the two clinical sites. Each site will have its own unique login credentials to REDCap, and each site will only be able to review its own study data. The REDCap database will be built and centrally monitored by the PASA DCC. The REDCap system goes through an internal User Acceptance Testing (UAT) phase to ensure it is bug-free and captures all appropriate study data prior to study launch.

Data cleaning in REDCap will be conducted on a regular basis to ensure the conduct of the trial follows the approved protocol, aligns with Good Clinical Practices (GCP) guidelines, and meets applicable regulatory requirements. Programmed system edit checks, manual edit checks, and ad hoc statistical reports will be generated to aid in the data cleaning process. The study audit trail is maintained within REDCap and captures all data changes made within the system including the date of the change, the original value, the new value, and the username of the individual making the change. Additionally, REDCap is built with branching logic and required fields to assigned variables to further increase data integrity.

All research staff entering data into REDCap are required to take a REDCap training course provided by the PASA DCC. All data management practices are outlined in the Data Management Plan (DMP).

### Confidentiality {27}

Study staff will maintain appropriate medical and research records for this study, in compliance with International Council for Harmonisation (ICH) E6 and regulatory requirements for the protection of confidentiality of participants. Physical research data will be stored in locked files in secure rooms at the UTHealth and UCLA sites, while electronic research data will be stored on locked computers on secure UTHealth and UCLA servers. Data will be kept for at least 7 years beyond the final publication date or submission to the FDA. De-identified data will be destroyed by shredding, and electronic data will be deleted from databases. Data and study files may be retained longer if required by other federal regulations or sponsor archive requirement.

Participant’s contact information will be securely stored at each clinical site for internal use during the study. Study participant research data will be transmitted to and stored at the PASA DCC. This will not include the participant’s contact or direct identifying information. Rather, individual participant research data will be identified by a unique study identification number. The REDCap system used by the study is secured, password-protected, and HIPAA-compliant.

To address concerns about confidentiality, the protocol team will obtain a Certificate of Confidentiality (CoC). CoCs allow researchers to refuse to disclose names or other identifying characteristics of research participants in response to legal demands.

### Plans for collection, laboratory evaluation, and storage of biological specimens for genetic or molecular analysis in this trial/future use {33}

Samples collected under this protocol will not be stored and will be analyzed immediately for participant health safety purposes and toxicology screens. Samples are destroyed after analysis.

## Statistical methods

### Statistical methods for primary and secondary outcomes {20a}

The study will test the single hypothesis that change in ISI score between baseline and day 14 differs between suvorexant and placebo at 14 days using a 0.05 significance level. We will also test treatment differences for five secondary measures: change in AUQ score, change in PCL-5 and CAPS-5 score, comparison of number of mean drinks per drinking day, and count of days with no alcohol consumption. Secondary analyses will be adjusted for multiple comparisons using the Benjamini-Hochberg false discovery rate correction to maintain the nominal alpha level of 0.05. All other statistical comparisons will be descriptive. All analyses will be based on the intention-to-treat population, and no other analysis populations are planned. All analysis and methods will be fully detailed in the study’s Statistical Analysis Plan (SAP).

For the primary outcome, comparison of the change in ISI score from baseline to day 14 between treatment groups will be analyzed using a linear model for continuous outcomes that accounts for treatment, site, sex, and baseline ISI score (see proposed model). Adjusted estimates of the change in ISI score between treatment and within treatment and corresponding 95% confidence intervals will be produced.$$\mathrm{Y}_{\mathrm{i}} = \upbeta_{0} + \upbeta_{1}\mathrm{Treatment}_{\mathrm{i}} + \upbeta_{2}\mathrm{Site}_{\mathrm{i}} + \upbeta_{3}\mathrm{Sex}_{\mathrm{i}} + \upbeta_{4}\text{Baseline ISI} + \epsilon_{\mathrm{i}}$$where *Y*_*i*_ is the change in ISI score from baseline to day 14, *β*_0_ is the intercept, *β*_1_ through *β*_4_ are coefficients, and *ε*_*i*_ is the error term which is assumed normally distributed.

A similar model will also be run for the secondary outcome of mean number of drinks per drinking day, while a Poisson model will be explored for the number and percent of days abstinent during the 13-day quit attempt period, accounting for treatment, site, sex, and baseline ISI score.

A mixed linear model for repeated measures will be used to estimate treatment differences for the change AUQ, PCL-5, and CAPS-5 scores from baseline to days 7 and 14. The model(s) will have fixed effects for treatment, time interval (as a categorical variable), treatment-by-time interaction, and the stratification effects of site, sex, and baseline ISI score. The baseline score for each outcome measure will also be included as a term in the model, as appropriate.

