### Objectives {7}

The primary objective of this study is to assess the initial efficacy of SUV (20 mg) in improving sleep metrics.

The secondary objectives of this study are:To assess the effect of SUV (20 mg) on cue-induced alcohol craving.To evaluate the effect of SUV (20 mg) on the mean number of drinks per drinking day.To evaluate the effect of SUV (20 mg) on drinks per day during the medication period over a 14-day quit attempt.To assess the initial efficacy of SUV (20 mg) in reducing PTSD symptoms.

The exploratory objectives of this study are:To assess the efficacy of SUV (20 mg) in improving sleep latency onset (SLO), wake after sleep onset (WASO), and total sleep duration via actigraph data.To evaluate the effect of SUV (20 mg) on National Institutes of Health Patient-Reported Outcomes Measurement Information System (PROMIS) sleep scale scores.

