### Outcomes {12}

The primary outcome is change in Insomnia Severity Index (ISI) score, measured as change from baseline to day 14.

Secondary outcomes include change in alcohol craving score from baseline to days 7 and 14, percent of total days abstinent during the 14-day practice quit attempt, mean number of drinks per drinking day as measured by the Timeline Follow Back, and change in PTSD symptoms as measured by change from baseline to days 7 and 14 in the CAPS-5 and PCL-5 score(s).

Exploratory outcomes include actigraphy sleep metrics for sleep latency onset (SLO), wake after sleep onset (WASO), and total sleep duration, as well as the change in PROMIS Sleep Disturbance *T*-score from baseline to day 14.

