### Methods in analysis to handle protocol non-adherence and any statistical methods to handle missing data {20c}

The intention-to-treat (ITT) population will be used for all planned analysis, with data from all participants analyzed according to the arm to which they were randomized irrespective of the amount of intervention received. This approach ignores noncompliance, protocol deviations, withdrawal, and lost-to-follow-ups. Analysis of the ITT population avoids overoptimistic estimates of the efficacy of an intervention resulting from the removal of non-compliers, accepting that protocol deviations occur in actual clinical practice.

Analysis of the secondary outcomes will be based on a mixed-effect model of repeated measures (MMRM) using data from all time points to account for missing data and thereby maximize information used for the analyses. These models treat missing data as ignorable missing, assuming any missing data are missing at random. No imputation processes will be used to replace missing data. However, every effort will be made to minimize missing data. Additionally, because missing observations have the potential to alter the results of analyses, we will examine whether the pattern of missing data is different among the groups.

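### Mean drinks per drinking day is a tested secondary outcome with no value for participants who stay abstinent, and the drinks-per-day objective that would count them is never tested

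*Protocol article*

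**What the plan says.** All references are to the protocol article.

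- **Trial design {8}**: after randomisation, participants try to stop drinking for two weeks.
- **Outcomes {12}** lists "mean number of drinks per drinking day as measured by the Timeline Follow Back" as a secondary outcome.
- **Statistical methods {20a}** names five tested secondary measures, corrected by Benjamini-Hochberg. Two concern drinking: "comparison of number of mean drinks per drinking day, and count of days with no alcohol consumption". For the first, "A similar model will also be run for the secondary outcome of mean number of drinks per drinking day". The model referred to is the primary one: treatment, site, sex, baseline ISI and normally distributed errors. The same section states: "All analyses will be based on the intention-to-treat population, and no other analysis populations are planned".
- **Protocol non-adherence and missing data {20c}** describes that population "with data from all participants analyzed according to the arm to which they were randomized irrespective of the amount of intervention received" and adds: "No imputation processes will be used to replace missing data".
- **Objectives {7}** has a further secondary objective: "To evaluate the effect of SUV (20 mg) on drinks per day during the medication period over a 14-day quit attempt". This quantity appears neither in Outcomes {12} nor among the five tests in {20a}.
- **Discussion** calls the alcohol outcomes effect-size generating rather than confirmatory.

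**The concern.** Drinks per drinking day is total drinks divided by number of drinking days. A participant who does what the trial asks has zero for both, so the outcome is undefined for the most complete response. Such participants are to be expected, because total abstinence is the requested behaviour and 48 hours of it is verified before randomisation.

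The model, the population and the no-imputation rule each make sense alone, but together they leave no stated place for this participant. If the abstainer leaves the model, the arms are compared within a group defined by post-randomisation drinking, which treatment is meant to change. Balance from randomisation no longer protects the comparison. The missing-data approach in {20c}, a repeated-measures model under missing at random, does not help: this outcome is one value per person, and the value is undefined rather than unobserved.

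At stake is an effect size meant to inform a larger trial. The Discussion says significant primary and/or secondary results are expected to justify one.

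**Working it through.** **Plan's own figures.** The plan gives no figure for this outcome and no expected proportion of full abstainers. The inputs taken from it are 76 randomised 1:1 (38 per arm) and at most 7% attrition (76 × 0.93 = 70.7, about 35 per arm). All drinking figures below are assumptions.

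**Illustration with two types of drinker.** Half are lighter (3 drinks per drinking day) and half heavier (8). On placebo, 20% of lighter and 5% of heavier drinkers abstain fully. Write the drinking fractions as L = 0.5 × (1 − lighter abstention) and H = 0.5 × (1 − heavier abstention). Then:

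- mean among drinkers = (3L + 8H) / (L + H)
- mean with abstainers coded 0 = 3L + 8H

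Placebo: L = 0.40, H = 0.475. With abstainers as 0: 1.2 + 3.8 = 5.00. Among drinkers: 5.00 / 0.875 = 5.71.

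(a) Suvorexant abstention 60% lighter and 10% heavier, continuing drinkers unchanged: L = 0.20, H = 0.45. With abstainers as 0: 0.6 + 3.6 = 4.20. Among drinkers: 4.20 / 0.65 = 6.46.

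(b) and (c) use the same abstention, with intake among continuing drinkers cut by 10% or 20%.

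(d) Abstention unrelated to drinking level (15% placebo, 40% suvorexant), intake cut by 10%. Among drinkers: 5.50 to 4.95. With abstainers as 0: 5.50 × 0.85 = 4.675 to 4.95 × 0.60 = 2.97.

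| Case | Difference among drinkers | Difference, abstainers = 0 |
|---|---|---|
| (a) no cut | 6.46 − 5.71 = +0.75 | 4.20 − 5.00 = −0.80 |
| (b) 10% cut | 5.82 − 5.71 = +0.10 | 3.78 − 5.00 = −1.22 |
| (c) 20% cut | 5.17 − 5.71 = −0.55 | 3.36 − 5.00 = −1.64 |
| (d) unrelated, 10% cut | 4.95 − 5.50 = −0.55 | 2.97 − 4.675 = about −1.70 |

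With the abstention pattern of (a) to (c), the sign turns at a cut of 1 − 5.714/6.462 = 11.6%. A larger reduction among continuing drinkers keeps the correct direction.

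**At the trial's size.** In case (a), 38 × 0.875 = 33 placebo and 38 × 0.65 = 25 suvorexant participants contribute. In 20,000 simulated trials (log-scale SD 0.35 within each drinker type), the estimate among drinkers had the wrong sign in 80% of trials and was significantly wrong-signed in 13%. In case (c) it had the wrong sign in 25%.

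**A second set of assumptions.** Log drinks per drinking day is 1.7 + 0.5s, with s standard normal. The logit of the daily chance of drinking is −0.8 + s, lowered by 0.8 on suvorexant, over 14 days.

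- With large extra person-to-person variation (beta concentration 1), full abstainers rise from 36% to 54% and drinks per day fall from about 2.7 to 1.8, while drinks per drinking day among drinkers rises from 7.2 to 7.8. About 38 of 70 participants remain.
- With no extra variation, abstainers are 6% and 16%, the rise is 6.41 to about 6.73, and about 62 of 70 remain.
- At concentration 1, a 10% cut among continuing drinkers removes the rise (7.21 to 6.99). If abstention is unrelated to drinking level, the measure is flat (6.20 and about 6.2).

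**If abstainers are coded 0.** Nobody is lost. In case (a), however, 12.5% of placebo and 35% of suvorexant values would sit exactly at zero (1 − 0.875 and 1 − 0.65), in a model assuming normal errors, and the quantity would no longer be drinks per drinking day.

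**The case against.** A reader might infer that the protocol excludes abstainers, and so breaks its own intention-to-treat rule and discards the best responders. The document does not say this. No section states that abstainers leave the model, and {20a} defers full detail to a statistical analysis plan that is not shown. The value for a participant with no drinking days is a derivation rule such a plan could supply. The no-imputation sentence does not settle it either, since it concerns missing data and an abstainer with a complete Timeline Follow Back has none missing. Coding abstainers 0 would keep everyone in.

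A reader might also infer that a real benefit would probably appear as harm, or that about half the sample would be lost. Both rest on assumptions: two of the four cases above show attenuation only, and the number remaining in the second illustration runs from about 38 to 62 of 70. In case (d) the result among drinkers is a fair account of the 10% cut; it simply gives no credit for abstention.

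In addition, days without alcohol is a tested measure, is defined for abstainers, and would register a drug that produces them.

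These points limit the severity but leave the core standing. The article itself fixes the endpoint, model, population and imputation rule, and they do not fit together for an expected kind of participant. Either reading has a cost: a selected subset, or a spike at zero under normal errors. Days abstinent carries no information on quantity. The untested drinks-per-day objective remains whatever the analysis plan says about abstainers.

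**Conclusion.** The point holds in conditional form. The outcome is undefined for full abstainers, and the stated model, population and no-imputation rule do not reconcile this. If abstainers drop out, the comparison is conditioned on a post-randomisation outcome and can understate a benefit: −0.55 against −1.64 or about −1.70 in the illustrations. Reversal (+0.75 against −0.80) requires both that extra abstention be concentrated in lighter drinkers and that continuing drinkers change little, by less than about 12% under the assumed mix. None of these drinking figures comes from the document.

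The mismatch between the drinks-per-day objective and the listed outcomes and tests needs no assumption. The matter should be fixed, but it touches one provisional secondary outcome and leaves the primary ISI analysis untouched.

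**What to change.** Before unblinding:

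1. Make drinks per day over the quit attempt, with full abstainers contributing 0, the tested consumption outcome in place of drinks per drinking day. It is already an objective, and the Timeline Follow Back already records daily quantity.
2. Analyse total drinks with a count model that allows overdispersion (negative binomial, for example), with log observed days as offset and treatment, site, sex and baseline ISI as terms. Baseline Timeline Follow Back drinking is an optional covariate.
3. Report drinks per drinking day descriptively among drinkers, with the number of full abstainers in each arm.
4. State the counting window once. The objective refers to a 14-day attempt, while {20a} refers to a 13-day period for days abstinent.

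The number of tested secondary measures stays at five. No new data are needed. The cost is that drinks per drinking day is no longer a tested outcome, and the protocol, analysis plan and registry wording must be updated.

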### Trial design {8}

This is a randomized, double-masked, placebo-controlled study to evaluate preliminary efficacy and safety of SUV (20 mg) for sleep disturbance in AUD and co-occurring PTSD symptoms in approximately 76 randomized men and women veterans and non-veterans between the ages 21 and 65. Following a 7-day placebo run-in, participants will be randomly assigned to receive SUV (10 mg (days 0–6) and 20 mg (days 7–13)) or matched placebo. Participants will be stratified on site, sex, and level of sleep disturbance (Insomnia Severity Index (ISI) score). Post-randomization, all participants will complete an alcohol cue-reactivity paradigm prior to the initial dose of study medication. The alcohol cue-reactivity paradigm is an established laboratory assessment of craving during which participants are exposed to real alcohol and water cues in a bar laboratory setting. Participants will then take their first dose of medication. Participants will begin the real-world practice quit attempt, during which they will attempt to stop drinking for 2 weeks. Participants will complete daily virtual diaries and visits to assess sleep, past-day drinking, and alcohol craving. Participants will return to one of the clinical sites on study day 14 to complete an alcohol cue-reactivity session, to assess post-medication craving. PTSD symptoms will be assessed via Clinician-Administered PTSD Scale for Diagnostic and Statistical Manual of Mental Disorders, Fifth Edition (DSM-5) (CAPS-5) and PTSD Checklist for DSM-5 (PCL-5) at baseline, at day 7, and at day 14 of treatment with SUV or matched placebo.

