#### Self-assessments

PCL-5: The PCL-5 is a 20-item self-report measure that assesses DSM-5-based criteria for PTSD symptoms. Each item is rated on a 5-point Likert-type scale (0 = not at all; 4 = extremely) that indicates how much the participant has been bothered by an identified “worst” stressful event in the past month [31].Insomnia Severity Index Score (ISI): This is a brief questionnaire to screen for insomnia in participants. A scoring system is used to identify what degree insomnia (if any detected) is affecting daily life and sleep patterns.Patient-Reported Outcomes Measurement Information System (PROMIS): This system provides clinicians and study research staff measures of mental and physical health and overall well-being from a patient perspective.Daily diary assessment: Participants will complete daily diary assessments reporting on their mood, alcohol and cigarette craving, motivation to change, self-efficacy, pain, and drinking behavior from the previous day. Participants will complete the DDA electronically during the practice quit attempt (days 0–14). Research staff will distribute the link to the online daily diary assessment during each in-person and virtual visit.

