## Discussion

Suvorexant (SUV) is a promising treatment for alcohol use disorder (AUD) and post-traumatic stress disorder (PTSD) due to the mechanism of action. Dual orexin receptor antagonism has demonstrated efficacy in restoring key sleep parameters in individuals with insomnia. Additionally, SUV has shown potential in preclinical studies to reduce alcohol self-administration and attenuate stress- and anxiety-like behaviors. The planned study will investigate the efficacy of SUV in improving sleep metrics, reducing alcohol craving, and alleviating PTSD symptoms in individuals with comorbid AUD and PTSD.

As of March 2025, and per ClinicalTrials.gov, the current study will be one of the first large-scale randomized clinical trials testing SUV in individuals with combined AUD and PTSD. This is a two-site trial, double-blind versus placebo with 1:1 randomization. Collection of laboratory-based alcohol-induced craving measures and PSG-validated actigraphy-based measures of sleep represents an innovative aspect of the study design, which seeks to elucidate mechanisms underlying the treatment effects without compromising the clinical trial design required to address the chief aims of sleep improvement and reduced drinking during a 14-day quit attempt. The potential of this trial to provide both initial efficacy signals and mechanistic insights for orexin-based AUD and PTSD pharmacotherapy stands to provide a justification for larger and longer multisite trials in this clinical population.

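### Poisson is the only model named for abstinent days, a count capped by the length of the quit attempt, and the analysis text uses a 13-day window where the outcome is defined over 14 days

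*Protocol article*

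**What the plan says.** In the protocol article, the section on statistical methods for primary and secondary outcomes {20a} lists five secondary measures to be tested. One of them is the "count of days with no alcohol consumption", and all five fall under a Benjamini-Hochberg correction at 0.05. The model for this measure is given in one clause: "a Poisson model will be explored for the number and percent of days abstinent during the 13-day quit attempt period", with terms for treatment, site, sex and baseline ISI. The section gives no alternative model and does not say how the variance is to be estimated. It refers to the SAP, which is not at hand, for full details.

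The Outcomes section {12} defines the same measure as "percent of total days abstinent during the 14-day practice quit attempt". Other sections agree with 14 days:

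- Objectives {7}: "drinks per day during the medication period over a 14-day quit attempt".
- Trial design {8}: participants start a quit attempt "during which they will attempt to stop drinking for 2 weeks", and dosing is "SUV (10 mg (days 0–6) and 20 mg (days 7–13)) or matched placebo", that is, 14 dates.
- Discussion: "reduced drinking during a 14-day quit attempt".

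Only {20a} says 13 days, and it gives no reason.

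**The concern.** There are two separate problems.

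**Model.** The number of abstinent days in a fixed window is a bounded, binomial-type count, and the corresponding percentage is not a Poisson variable at all. Poisson regression can still estimate a ratio of means for such data. Its model-based standard error, however, is right only if the variance happens to equal the mean. Otherwise the confidence interval is too wide or too narrow, and the p-value passed to the Benjamini-Hochberg procedure is miscalibrated. That p-value can also affect whether the other four measures are declared significant. The Discussion calls these outcomes effect-size generating, so the interval is what a later trial would use.

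**Window.** An analyst cannot follow both {12} and {20a}. It is unclear which day is left out, and the percentage reported for a given participant depends on the answer.

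**Working it through.** **Inputs.** The window is m = 14 days (Outcomes {12}; dosing on days 0 to 13). About 35 participants per arm are analysed, because 76 × 0.93 = 70.7 after the 7% attrition in Sample size {14}. The protocol gives neither p, the proportion of days abstinent, nor ρ, the correlation between days within a person. Both are assumptions here and are shown as ranges. The protocol states no power or precision for this outcome, so there is no figure to reproduce.

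**Variance.** With mean mp:

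- Poisson variance: mp.
- Bounded count with within-person correlation: mp(1−p)[1+(m−1)ρ].
- Ratio for m = 14: φ = (1−p)(1+13ρ).

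The true standard error of the log rate ratio is √φ times the model-based Poisson standard error. The actual type I error of a nominal 5% Wald test is therefore about 2[1−Φ(1.96/√φ)].

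| p | ρ | φ | √φ | Type I error, formula | Type I error, simulated |
|---|---|---|---|---|---|
| 0.5 | 0 | 0.50 | 0.71 | 0.6% | 0.5% |
| 0.5 | 0.2 | 1.80 | 1.34 | 14.4% | 14.6% |
| 0.5 | 0.4 | 3.10 | 1.76 | 26.6% | 26.6% |
| 0.5 | 0.6 | 4.40 | 2.10 | 35.0% | 35.4% |
| 0.7 | 0 | 0.30 | 0.55 | <0.1% | 0% |
| 0.7 | 0.2 | 1.08 | 1.04 | 5.9% | 6.0% |
| 0.7 | 0.4 | 1.86 | 1.36 | 15.1% | 15.0% |
| 0.7 | 0.6 | 2.64 | 1.62 | 22.8% | 22.9% |
| 0.8 | 0 | 0.20 | 0.45 | <0.1% | 0% |
| 0.8 | 0.2 | 0.72 | 0.85 | 2.1% | 2.1% |
| 0.8 | 0.4 | 1.24 | 1.11 | 7.8% | 8.0% |
| 0.8 | 0.6 | 1.76 | 1.33 | 14.0% | 13.8% |

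The simulated column uses beta-binomial data with no treatment effect, 35 per arm, 20,000 replicates and no covariates. In the same runs a quasi-binomial test rejected 4.3% to 5.1% of the time. A separate set of 3,000 to 4,000 runs (p 0.6 to 0.8, ρ 0 to 0.5, m = 13 or 14) gave 3.6% to 6.3% for quasi-binomial and robust-variance Poisson tests taken together.

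**Break-even.** φ = 1 when ρ = p/[13(1−p)]. This is 0.08 at p = 0.5, 0.18 at p = 0.7 and 0.31 at p = 0.8. Below that value the Poisson test is conservative, and above it the test rejects too often.

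**Upper bound.** A Poisson variable with mean 14 × 0.8 = 11.2 has probability 0.16 of exceeding 14, which is impossible for this outcome.

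**Window.** Days 0 to 13 are 14 dates, and days 1 to 13 are 13. Take a participant abstinent on 10 of 14 days, which is 71.4%. If the dropped day was a drinking day, the result becomes 10/13 = 76.9%. If it was an abstinent day, it becomes 9/13 = 69.2%.

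**The case against.** The other side has several good arguments.

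- **The model is not firmly fixed.** The Poisson model is only to be explored, whereas firmer wording is used for the primary analysis, and details are left to the SAP. This stands as a limit on the claim. Poisson is nevertheless the only model named for a measure that will be formally tested.
- **The miscalibration comes from the model-based variance, which the text neither states nor excludes.** This also stands. Robust variance in a Poisson model would largely cure the problem, so choosing a logistic model over it is partly preference.
- **Size and direction are unknown.** Correct. The highest error rates need p = 0.5 with strong clustering, and some plausible combinations give close to 5%.
- **Thirteen days may be deliberate.** The TLFB description limits that measure to days outside test sessions, and day 0 is a cue-reactivity day, so days 1 to 13 may be meant. The text does not say so. The right request is therefore to reconcile the sections, not to declare one of them wrong.
- **The outcome is secondary and described as provisional.** Correct, and this limits the severity.

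A reader might also infer three stronger points that the protocol does not support.

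- **That dropouts are scored as drinkers.** Section {20c} rules out imputation, and an offset or denominator may be in the unseen SAP.
- **That the diary adds a third, 15-day window.** The diary runs on days 0 to 14, but each entry reports the previous day, so entries on days 1 to 14 cover days 0 to 13.
- **That the 13/14 conflict changes every participant's percentage.** With numerator and denominator on the same days, 0% and 100% do not move, and a constant window length cancels from a rate ratio.

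**Conclusion.** The point holds at moderate weight and should be fixed. The protocol names a model whose default variance does not suit a bounded count, for a measure that enters the secondary multiplicity family. If model-based Poisson variance is used, type I error at a nominal 5% lies anywhere from about 0% to about 35% over p of 0.5 to 0.8 and ρ of 0 to 0.6. Those ranges are assumptions, and the protocol does not show where in them the trial will fall. It would be too strong to say that the error bars will be wrong: the text allows the error without establishing it.

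The window conflict between {12} and {20a} needs no assumption. Its effect is on the reported percentages and on which day is counted, and it has little bearing on a rate ratio. The primary ISI comparison is untouched.

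**What to change.** 1. Analyse abstinent days out of days observed with a quasi-binomial or beta-binomial logistic model. Keep the planned terms (treatment, site, sex, baseline ISI) and optionally add baseline percent days abstinent, which the 30-day pre-study TLFB supplies. If a rate ratio is preferred, the minimum is Poisson with a log days-observed offset and robust variance, both stated.
2. Reconcile Outcomes {12} and Statistical methods {20a} to one named set of calendar days, used for both numerator and denominator. If a day is left out on purpose, say which day and why.

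The cost is a wording change in the protocol and SAP before unblinding, with no new data. Under the logistic models the effect is reported as an odds ratio, or as a difference in percent days abstinent, instead of a rate ratio.
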